#### Intervention

Subjects in the placebo group received a single dose of 0.9% sodium chloride (8.2 mL) as the placebo, which was administered as a bolus injection intravenously over 5 min at 8 h post-baseline (0 h). Subjects in the intervention group received a single dose of dexamethasone 8.25 mg (2.5 mL) made up to 8.2 mL with 0.9% sodium chloride, which also was administered as a bolus injection intravenously over 5 min at 8 h post-baseline (0 h).

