##### Hypoxication

Following the assessment at hour 0, participants experienced 24 h of normobaric hypoxia at specific oxygen concentrations using a hypoxication tent (Everest Summit Hypoxic Generator, Hypoxic Systems, New York). The hypoxication tent is a self-contained structure measuring approximately 2 m (w) × 2.5 m (l) × 1.8 m (h), in which the oxygen levels are tightly controlled. Participants may leave the tent during the intervention, during which time they will wear a mask attached to a portable hypoxicator to make sure the inspired oxygen concentrations are controlled. Participants will continue with normal activities while in the tent, such as eating and sleeping. The time from which the participant begins to inspire hypoxicated air (FiO_2_ 12%) marks the start of hour 1. Subsequent observations were taken on the hour, plus or minus 30 min to allow for any unanticipated delays during the study visit. At hour 25, the participant returned to breathing oxygen at normal atmospheric pressure (FiO_2_ 21%). The hypoxication schedule is shown in Table 3.

**Table 3 Tab3:** Schedule of participant hypoxication

Timeline	Inspired oxygen concentration (FiO_2_)
Baseline	Normal atmospheric O_2_ (21%)
Hours 1–12	12%
Hours 13–21	13.5%
Hours 22–24	12%
Hours 25–26	Normal atmospheric O_2_ (21%)

Three hypoxic generators were used to control the environment. Carbon dioxide build-up was controlled with an air pump (Bair Hugger™, 3M, Berkshire, UK). Air from the tent was pumped through two soda lime scrubbers (Spherasorb™, medical grade soda lime from Intersurgical Ltd, UK, in canisters by Draeger Medical UK Ltd). These were replaced after 12 h.

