##### Statistical analysis plan

As in Sagoo et al. [3], it thought plausible to assume that the outcomes would be normally distributed. We will assess this assumption using the residuals from models that assume the data are normally distributed. If the residuals are not normally distributed, we will transform the raw data and repeat the normality assumption check.

Ultimately the primary aim of the study is to compare outcomes between placebo and dexamethasone groups at 22 h. The comparisons could be made by performing *t*-tests using data collected at 22 h. This is, however, inefficient and so potentially to increase power, we will include outcome measures for all time points. To account for the correlation among measurements taken from the same volunteer at multiple time points, we will analyse data by fitting linear mixed models. Separate linear mixed models will be fitted for different outcomes. Each linear mixed model will include a fixed term(s) for the time at which a measurement was taken, a fixed term for the treatment group of the volunteer and an interaction term for time and treatment group. The interaction term enables us to make inference for the mean difference between the placebo and dexamethasone groups at different time points. If there is an imbalance of a baseline characteristic, a fixed term for the characteristic will be included in the model. Outcome measurement profiles over time will be assessed first. If the relationship is approximately linear, a linear term for time will be fitted. If not, time will be taken as a categorical variable.

For data taken at 22 h, we will report the estimated mean differences, the 95% confidence interval for the mean differences of the primary outcome measures and *p* values to test the hypothesis that the mean difference is zero. As mentioned previously, because this is a pilot study, the hypothesis will be tested at a 20% significance level. Also, for the same reason, we will not adjust for multiple hypotheses (corresponding to different outcome measures).

The above analysis plan will be used if it is plausible to assume that the data are normally distributed. If a transformation does not achieve normality, we will use non-parametric methods such as the Mann–Whitney U test.

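### The option to fit time as a straight line forces the arm difference onto one line from 0 to 26 h, which cannot represent a drug given at hour 8 and can shrink the 22 h estimate

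*Protocol article*

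**What the plan says.** The section headed Statistical analysis plan names the target: "Ultimately the primary aim of the study is to compare outcomes between placebo and dexamethasone groups at 22 h". To gain power over a simple comparison at that hour, it says "we will include outcome measures for all time points", using a linear mixed model for each outcome. Besides time, the model has "a fixed term for the treatment group of the volunteer and an interaction term for time and treatment group", and "The interaction term enables us to make inference for the mean difference between the placebo and dexamethasone groups at different time points".

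The form of time is decided after looking at the outcome profiles: "If the relationship is approximately linear, a linear term for time will be fitted". The alternative follows at once: "If not, time will be taken as a categorical variable".

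The design sections fix the timing. The Intervention section puts the single injection at hour 8. The Abstract and the Clinical assessments section put the MRI scans at 0, 7, 11, 22 and 26 h. The Hypoxication section states: "At hour 25, the participant returned to breathing oxygen at normal atmospheric pressure". Table 3 gives inspired oxygen of 21, 12, 13.5, 12 and 21% over the visit.

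**The concern.** If time is linear, the time-by-treatment term is a single slope, so the modelled arm difference is an intercept plus that slope times the hour. The schedule rules this shape out for any real effect. Before hour 8 neither arm has received drug, so randomisation makes the expected difference zero at 0 and 7 h, and a straight line that is zero at two times is zero everywhere. At the other end, the 26 h scan is taken in normoxia, when the arms may have converged for reasons unrelated to the drug effect at 22 h.

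The 22 h value read off the line is therefore a mixture of pre-dose, post-dose and recovery data. At stake are the main estimate of the trial, the 95% confidence interval promised for it, and the power that the mixed model was meant to add.

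**Working it through.** The article gives no figure of its own for this point, so the check works from the schedule.

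**Weights.** With complete data at common times and a random intercept, the fixed effects equal those of least squares. The linear estimate of the difference at 22 h is the sum of w(j) × d(j), where d(j) is the true difference at time t(j) and

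w(j) = 1/k + (22 − m)(t(j) − m)/S.

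Here k is the number of times, m their mean and S the sum of squared deviations. For MRI, k = 5, m = 66/5 = 13.2 and S = 458.8. For 26 h: 0.2 + 8.8 × 12.8/458.8 = 0.446. For 22 h: 0.2 + 8.8 × 8.8/458.8 = 0.369. The full set for 0, 7, 11, 22 and 26 h is −0.053, 0.081, 0.158, 0.369 and 0.446. With categorical time, the weight is 1 on 22 h and 0 elsewhere.

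**Share of the true 22 h effect recovered (MRI).** The article gives no time course for the arm difference, so these profiles are assumptions, scaled to 1 at 22 h.

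| Difference at 0, 7, 11, 22, 26 h | Linear estimate at 22 h |
|---|---|
| 0, 0, 1, 1, 1 (persistent step) | 0.158 + 0.369 + 0.446 = 0.97 |
| 0, 0, 0.5, 1, 1 | 0.89 |
| 0, 0, 0, 1, 1 | 0.81 |
| 0, 0, 0.5, 1, 0.5 (half convergence) | 0.079 + 0.369 + 0.223 = 0.67 |
| 0, 0, 1, 1, 0 | 0.53 |
| 0, 0, 0.5, 1, 0 (full convergence) | 0.079 + 0.369 = 0.45 |
| 0, 0, 0, 1, 0 | 0.37 |

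The direction is usually towards zero, but not always: an effect present only at 11 h (0, 0, 1, 0, 0) yields a spurious 0.16 at 22 h. If every d(j) is zero, the estimate is zero and the form introduces no bias.

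**Lake Louise score.** The Clinical assessments section lists hour 26; Table 2 shows no score then. Hour 0 is included and hour 8 is treated as pre-dose.
- With hour 26 (times 0, 2, 4, 6, 8, 11, 22, 26) and half the effect at 11 h, the estimate is 0.66 with half convergence and 0.44 with full convergence. With a persistent step it is 0.95.
- Without hour 26 it is 1.08, 0.93 or 0.79 when the effect at 11 h is full, half or absent.

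**What this means for whole-brain ADC.** Table 1 gives a difference of 0.5 and SD of 0.45. Assume 10 per arm (20 volunteers split equally), two-sided alpha 0.20, within-subject correlation 0.5 and a normal approximation.
- 22 h data alone, or unconstrained categorical time: SE = 0.45 × √(2/10) = 0.201; power = Φ(0.5/0.201 − 1.282) = 88.6%. (Table 1 prints 93% without its sample size; 12 per arm gives 92.5%. Nothing here depends on that.)
- Linear time: the relative variance is ρ + (1 − ρ) × Σw², with Σw² = 0.369. At ρ = 0.5 this is 0.684, so SE = 0.201 × √0.684 = 0.166. Power is 94.9% for the persistent step, with 94.9% coverage of the 95% interval. For 0, 0, 1, 1, 0 power is 61.8% and coverage 70.5%.

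**Does the look at the profiles protect the estimate?** A simulation took 10 per arm, SD 0.45, correlation 0.5 and a true 22 h difference of 0.5. It applied an assumed 5% lack-of-fit test as the linearity check.

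| Placebo course | Linear form kept | Mean linear estimate |
|---|---|---|
| Linear to 26 h | 94% | 0.49 |
| Half recovery at 26 h | 75% | 0.34 |
| Full recovery at 26 h | 39% | 0.22 |
| Full recovery, arms differ only at 22 h | 20% | 0.19 |

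**Precision of the fix against linear time.** Under compound symmetry with known covariance, using the two pre-dose scans gives relative variance 1 − 2ρ²/(1 + ρ).

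| ρ | Categorical, pre-dose values used | Linear |
|---|---|---|
| 0.3 | 1 − 0.18/1.3 = 0.86 | 0.3 + 0.7 × 0.369 = 0.56 |
| 0.5 | 1 − 0.50/1.5 = 0.67 | 0.68 |
| 0.7 | 1 − 0.98/1.7 = 0.42 | 0.7 + 0.3 × 0.369 = 0.81 |

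**The case against.** The strongest reply is that the plan already has a safeguard: time becomes categorical when profiles are not roughly linear. A reader might infer from the 45% figure that the trial stands to lose more than half of its effect. The documents do not support that. The figure needs the linear branch to be chosen and the arms to converge fully by 26 h, which is the rise-and-fall profile most likely to be sent to categorical time. Where the simulated check kept the line most often, the mean estimate was almost right. This part of the objection stands and limits the size. It does not remove the point, because under half recovery the line was kept in 75% of runs and the estimate averaged 0.34 against 0.50. The rule as worded also concerns the outcome's course over time, and a straight course does not make the arm difference straight.

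Four further limits stand:
- The 22 h value is interpolated, since 22 h lies inside the observed range.
- The choice of form is a stated, data-dependent rule, so it should not be read as an unplanned choice. A numerical criterion for linearity may properly sit in an analysis plan that is not shown, and its absence is not part of this point.
- The linear form can be more precise: it has more power for a persistent step than unconstrained categorical time.
- The study is a declared pilot, tested at 20% without multiplicity adjustment. That tempers the consequence, but the plan still promises a 95% interval for the 22 h difference.

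**Conclusion.** The point holds, conditionally. The linear branch is a stated option that cannot represent a drug effect beginning at hour 8, and for MRI it gives the normoxic 26 h scan more weight than the 22 h scan. If that branch is used, the 22 h estimate is usually pulled towards zero: about 3% for a persistent step, about a third with half convergence, and 55% in a near-worst case. For the Lake Louise score the bias is large only if hour 26 is collected; without it the estimate is about 79 to 108% of the truth.

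The mechanism and weights follow from the schedule, given complete data and a random intercept. The sizes rest on assumed effect profiles; the power, coverage and precision figures also rest on an assumed correlation, and the retention rates on an assumed lack-of-fit check. It would be too strong to say that the 22 h comparison is biased as planned: there is none of this bias under categorical time, or if the drug has no effect at any time.

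**What to change.** Delete the linear option. State that time is categorical for every outcome, that the arms are constrained to a common mean at pre-dose times (or that the model adjusts for the pre-dose values), and that the 22 h difference is estimated directly as a contrast. Also reconcile the Clinical assessments section with Table 2 on whether the Lake Louise score is taken at hour 26.

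The cost is about one sentence of text and a few more fixed-effect parameters. All time points can still be used, as the plan intends. Compared with linear time, precision is lost at low within-subject correlation (relative variance 0.86 against 0.56 at 0.3), about equal at 0.5, and gained at 0.7 (0.42 against 0.81). No study procedure changes.

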#### Participant withdrawal criteria

A participant would be withdrawn from the study during the interventional visit in the following circumstances:
If the participant scores ‘severe’ for more than one symptom on the Lake Louise Mountain Sickness Score Questionnaire.If it becomes medically necessary in the opinion of the clinician overseeing the study visit.The participant requests to be withdrawn at any time.

In the event of withdrawal, the researcher will record the reason for discontinuation and any AEs in the participant’s notes.

#### Trial stopping rules

The trial will be stopped if:
A serious adverse reaction occurs that may be related to the administration of the IMP to a participant.A severe non-serious adverse reaction occurs that may be related to the IMP, regardless of the system and organ class, to two participants.

In these circumstances, the trial steering committee, data-monitoring committee, sponsor, research ethics committee and the Medicines and Healthcare Products Regulatory Agency will be notified within 24 h of receipt of the initial report. Any participants actively involved in the trial will be withdrawn and all trial activities will be immediately discontinued.

#### Participant safety

A clinical member of the study staff was present in the study area at all times during the interventional study visit. Participants’ vital signs were monitored throughout the intervention period, except for hours 12–21, when it was expected that the participant would be sleeping, unless the participant became unwell. A thorough risk assessment of the study area was undertaken and approved. Unblinding of investigators and participants is permitted in the event of any AE, serious adverse event (SAE) or suspected unexpected serious adverse reaction (SUSAR). Unblinding will take place via codebreak envelopes stored within the MRI suite and pharmacy at UHCW.

#### Trial oversight

Trial oversight is provided by the trial management group. The trial steering committee will meet regularly to review progress and the safety of the study. There is also an independent data management group. The study sponsor, UHCW, is a National Institute for Health Research facility. The study was reviewed after the first two participants to ensure the safety and quality measures were met. After 20 patients had completed the protocol, a preliminary analysis was performed, and if sufficient differences had been seen, the study would have been closed to recruitment. If not, recruitment will continue to 30 patients. All potential AEs, as defined by good clinical practice (AEs, SAEs or SUSARs), were compiled by the trial manager and statistician and reviewed by the sponsor. All Grade IV AEs, all SAEs and all SUSARs were reported to the trial management group within 24 h. Participant information will be held securely at the trial sponsor site until study closeout, when they will be transferred to a third-party storage facility with appropriate security, and fire and flood provisions.

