**Methods/design:**

D4H is a double-blind placebo-controlled randomised trial assessing the effect of dexamethasone on hypoxia-induced cerebral oedema. In total, 20 volunteers were randomised in pairs to receive either 8.25 mg dexamethasone or normal saline placebo intravenously after 8 h of hypoxia with an FiO_2_ of 12%. Serial MRI images of the brain and spinal cord were obtained at hours 0, 7, 11, 22 and 26 of the study along with serum and urinary markers to correlate with the severity of cerebral oedema and the effect of the intervention.

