#### Sample size

Estimates from our previous observational study of MRI differences at normobaric hypoxia were used to determine the power [3]. It was assumed that dexamethasone will reverse outcome measures to their baseline values. Powers for pairwise comparisons at 22 h for three different significance levels (0.05, 0.10 and 0.20) and for three outcome measures that showed change at 22 h from baseline in the observational work were calculated by assuming that the data are normally distributed, (Table 1). Since most of the other outcomes showed smaller differences, it was decided to test hypotheses at 20% significance and make this study a pilot study.

**Table 1 Tab1:** Power for different outcomes and significance levels

Outcome	Estimates from Sagoo et al. [3]		Power		
	Difference	Standard deviation	α = 0.05	α = 0.10	α = 0.20
Blood oxygen content, ml O_2_/dL blood	2.05	1.33	97	98	99
Whole-brain ADC × 10^–4^/mm^3^	0.5	0.45	78	86	93
Corpus callosum (genu) ADC × 10^–4^/mm^3^ (mean of right and left)	1.35	1.65	52	64	77

*ADC* apparent diffusion coefficient

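### The outcome-driven option to stop at 20 volunteers or go on to 30 is not reflected in the unadjusted 20% test, so the error rate delivered depends on an undefined threshold

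*Protocol article*

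**What the plan says.** Three parts of the protocol article bear on this point.

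- **Trial oversight** describes a look at the data once 20 volunteers have finished, with this consequence: "if sufficient differences had been seen, the study would have been closed to recruitment. If not, recruitment will continue to 30 patients". It names no outcome, threshold or division of the significance level. Safety stopping has its own section (Trial stopping rules), and the early check of safety and quality is a separate review after the first two participants.
- **Sample size** explains the lenient level: most other outcomes had shown smaller differences, so "it was decided to test hypotheses at 20% significance and make this study a pilot study". It mentions neither a look at 20 nor an extension.
- **Statistical analysis plan** sets the comparison of placebo and dexamethasone at 22 h, with p "values to test the hypothesis that the mean difference is zero", and says that "the hypothesis will be tested at a 20% significance level". On multiplicity its one statement is "we will not adjust for multiple hypotheses (corresponding to different outcome measures". It does not refer to the preliminary analysis.

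The abstract gives only the smaller number: "In total, 20 volunteers were randomised in pairs".

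**The concern.** In a placebo-controlled trial whose safety rules are set out elsewhere, closing recruitment because sufficient differences were seen reads as a decision on comparative outcome data. A favourable result at 20 ends the trial, and an unfavourable one earns 10 more volunteers and another analysis. If the final analysis keeps the whole 20%, a false positive can arise on either occasion and the total exceeds 20% by an amount that the document does not fix.

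Pilot status does not remove the problem. A lenient level is a legitimate choice for a pilot, but readers will take 20% as the rate delivered. The article still tests hypotheses with p values, and its Discussion makes further studies in patients depend on a clear benefit. The waiver of adjustment is limited to different outcome measures and so does not cover looking twice at one outcome.

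**Working it through.** **The plan's own figures.** The article gives no two-look error rate to reproduce. Its only design calculation is Table 1, which states power without a sample size. For whole-brain ADC (difference 0.5, SD 0.45) Table 1 gives 78, 86 and 93% at levels 0.05, 0.10 and 0.20. The two-sided normal approximation gives:

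- 10 per arm: 70.0, 79.9 and 88.6%
- 12 per arm: 77.7, 85.9 and 92.5%
- 15 per arm: 86.1, 91.9 and 96.1%

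Over all nine cells of the table, 12 per arm agrees within 0.5 points. Table 1 thus fits a single two-sided analysis of about 24 volunteers (about 26 if t-tests were used). It matches neither 20 nor 30, and nothing in it allows for an interim look.

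**Inputs for the two-look error**

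- First look at 20 and maximum of 30 (Trial oversight).
- Final test at 0.20 (Statistical analysis plan).
- Two-sided: assumed, because the null is a zero difference and because Table 1 fits two-sided tests.
- 1:1 allocation, hence 10 then 15 per arm: assumed, as the ratio is not stated.
- Interim threshold α₁: not stated, so varied.

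**Formula.** With information fraction 20/30 = 0.667, the two test statistics have correlation √0.667 = 0.816 under the null. For two-sided critical values c₁ and c₂,

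overall error = 1 − P(|Z₁| < c₁ and |Z₂| < c₂).

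This was computed from the bivariate normal distribution and checked by simulating two-sample t-tests on nested data (10, then 15 per arm).

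| Interim threshold | Final test | Overall error, normal | Overall error, t-test simulation |
|---|---|---|---|
| p<0.20 | p<0.20 | 28.4% | 28.5% |
| p<0.10 | p<0.20 | 22.7% | 23% |
| p<0.05 | p<0.20 | 20.8% | 21% |
| p<0.01 | p<0.20 | 20.04% | about 20% |

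In the first row the excess over the stated level is 28.5 − 20 = 8.5 percentage points per outcome. In the last row it is negligible.

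**Levels that hold 20% overall.** Solving the same formula for an overall error of 0.20 gives:

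- equal levels (Pocock type): 0.137 at each look by the normal calculation, 0.136 in the t-test simulation;
- stricter first look (O'Brien-Fleming type): 0.094 at 20 and 0.171 at 30 by the normal calculation. In a t-test simulation at these small sizes, 0.09 then 0.17 gives 20.0%.

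Thirty volunteers randomised in same-arm pairs make 15 pairs, so an equal split is not attainable. With 16 against 14 at the end, the first-row figure stays at 28.5%.

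**The case against.** The strongest reply is that 28.5% rests on an assumption. The article attaches 20% to the planned analysis and gives no level for the look. With a strict threshold such as p<0.01 at 20, the final 20% test is practically intact. That stands, and it is why the result is given as a range. It does not dispose of the point, because the article leaves the threshold open while fixing the final test at the full 20%.

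A second reply is that an unseen full protocol or analysis plan may define the rule. That also stands: a reader might infer that the trial has no error control at all, and a condensed article cannot show this. What can be said is that the sections shown here do not fit together.

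Three stronger readings are tempting and are not supported.

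- *Some outcome will almost always look different at 20.* With 11 independent outcomes, 1 − 0.8¹¹ = 91% would show at least one p<0.20 under no effect. This is multiplicity across outcomes, which the article openly waives, and it would be the same without a look. The count of 11 is also a reader's own, since the objective refers to prespecified MRI parameters without listing them. Nothing says that any single outcome can trigger closure.
- *Stopping at 20 grossly exaggerates the effect.* For an assumed true effect of 0.5 SD, trials that stop on p<0.20 report 0.87 SD on average. That is selection on significance at N = 20, and a fixed trial of 20 reported only when p<0.20 shows the same. Averaged over all trials under this design the estimate is 0.55 SD. The 0.5 SD is not from the documents either: Table 1 implies 0.5/0.45 = 1.11 SD for whole-brain ADC.
- *The 95% interval contradicts the rule for stopping.* The article does plan "the 95% confidence interval for the mean differences of the primary outcome measures" beside a 20% test, but no passage says that either one governs the look. This is a separate matter of presentation.

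**Conclusion.** The point holds in limited form. The article combines an outcome-dependent stop at 20, an extension to 30 and an undiminished 20% final test, and its multiplicity waiver does not reach repeated looks. The stated level is held only if the unstated interim threshold is very strict. The per-outcome type I error runs from about 20% (look at p<0.01) to about 28.5% (look at the protocol's own 20%), assuming two-sided tests, 1:1 allocation and t-tests at 10 then 15 per arm. The planned mixed models would shift these figures somewhat.

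A reader might infer that the true level simply is 28.5%, but that is only the figure for a look at the 20% level. If the look used a pooled, blinded change from baseline there would be no inflation, though the text does not say so. Since the trial is declared a pilot, accepts false positives openly and leads to further studies rather than to practice, this is a should-fix matter of clarification, not a fatal flaw.

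**What to change.** Choose one of two routes and state it in the Sample size, Statistical analysis plan and Trial oversight sections alike.

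1. **Fixed size.** Set one sample size and make any look at 20 non-comparative, confined to safety and data quality. The final 20% test then stands as written. The cost is the option to stop early. If the size is fixed at 30, it also costs up to 30 − 20 = 10 volunteers compared with a trial that would have closed at 20.
2. **Two looks with a rule.** Name one decision outcome at 22 h and split the 20% over the looks: about 0.136 at each, or a stricter first look of about 0.09 then 0.17. Apply the boundary to the planned 22 h contrast from the mixed model, and recompute it if the allocation or information fraction differs from that assumed here. State who sees unblinded results. The Randomisation section already places an unblinded statistician outside the trial management group. The cost is a slightly stricter level at each look.

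The article reports the look in the past tense. If it has been made, neither route can be adopted retrospectively. The report should then describe the look, the outcome and threshold actually used, and the two-look error beside the nominal 20%.

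Whichever route is taken, state the sample size behind Table 1, and reconcile it with the 20 in the abstract and the 30 under Trial oversight. This is wording only.
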